## Methods/Design

### Study design

A 16-week parallel, double-blind, randomized, placebo-controlled dietary supplementation trial will be conducted in the Respiratory Medicine department at the Repatriation General Hospital (RGH), Adelaide, South Australia in collaboration with the Nutritional Physiology Research Centre (NPRC), University of South Australia, Adelaide, South Australia and the Clinical Nutrition Research Centre, University of Newcastle, Callaghan, NSW. Participants will attend the RGH on two occasions (pre- and post-intervention) for a series of tests including pulmonary function, venepuncture, well-being questionnaires and functional exercise capacity (see Figure 1).

**Figure 1 F1:**
[figure not shown]
Study overview.

### Participants

Participants will be recruited from the respiratory trials database (which contains >500 people who have previously indicated their willingness to be contacted for future studies) at the RGH. To be eligible for inclusion, participants are required to be adults (≥18 years of age), have a clinical and spirometric diagnosis of COPD (FEV_1_/FVC <0.7) based on GOLD criteria [1], and stable medication for 28 days prior to screening. Participants will be excluded from the study if they habitually consume LCn-3PUFA supplements, have unstable or very severe COPD (FEV_1_ <30% predicted) [1], have a diagnosis of α-antitrypsin deficiency, are a current smoker, are cachexic (unintentional weight loss of >5% within 12 months [28] or have a body mass index (BMI) ≤18.5 kg/m^2^), are morbidly obese (BMI ≥40 kg/m^2^), are experiencing unstable comorbidities (for example, right heart failure, sleep disorders), have used systemic steroids or antibiotic medication within 28 days prior to enrolment, are diagnosed with respiratory conditions not related to airflow limitation (for example, pulmonary fibrosis), have unstable medication use (change in medication or use in the 6 months prior to enrolment), have participated in a comprehensive pulmonary rehabilitation program in the previous 2 years or are intending to undertake this type of rehabilitation program in the 6 months following study enrolment. Written informed consent will be obtained from all participants.

### Ethics and Trial registration

Ethics approval for this study was granted by the Human Research Ethics Committee of the University of South Australia (project number: 0000026302) and Southern Adelaide Clinical Human Research Ethics Committee (project number: 208.12). The trial was registered on the Australia and New Zealand Clinical Trials registry (ANZCTR) on the 3rd of February 2012 (ANZCTR Number: 12612000158864).

### Sample Size

As this is a feasibility study designed to determine pragmatic aspects of methodology, formal sample size calculations are not appropriate [26,29]. The target sample size for the feasibility study is 40 participants. The target sample is to allow sufficient precision to enable sample size calculations for subsequent studies. Browne [30] suggests that a minimum of 30 participants is required to achieve sufficient precision, a recommendation supported by Lancaster *et al*. [31]. The target sample of 40 enrolled participants will allow completion of 30 subjects, allowing for a 25% participant dropout rate. A key feasibility criterion is the ability to recruit a target sample of 40 participants within 52 weeks.

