**Methods/Design:**

A 16-week parallel, double-blind, randomized, placebo-controlled dietary supplementation trial will be evaluated. Forty participants meeting spirometric and clinical criteria for COPD will be recruited from metropolitan Adelaide, South Australia. Participants will be randomized by minimization, based on a score derived from the modified Medical Research Council Scale for breathlessness, to receive 6 g/day of fish oil (approximately 3.6 g/day of LCn-3PUFA), or placebo (6 g/day of corn oil) capsules. Feasibility outcomes (recruitment, retention, supplement adherence, and time lost to exacerbation) and scientific outcomes (effect size and estimates of variance for inflammatory biomarkers, incorporation of LCn-3PUFA into erythrocytes, small airways function, dyspnea and functional exercise capacity) will be assessed pre- and post-intervention. Key feasibility criteria include recruitment of 40 participants in 52 weeks, 75% participant retention rate, 2% increase in the proportion of long-chain omega-3 fatty acids in erythrocytes, and a positive moderate effect size in at least three efficacy measures.

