### Feasibility outcomes and criteria

Within the four domains of feasibility (process, resources, management and scientific) there are specified outcomes in the process and resource domains that will be assessed throughout the study against feasibility criteria (see Table 2).

**Table 2 T2:** Feasibility outcomes and key feasibility criteria

**Outcome**	**Outcome measure**	**Key feasibility criteria**
*Process*		
Recruitment rate	Number of participants recruited per week.	Recruit 40 participants in 52 weeks.
Retention rate	Number of participants completing the intervention.	Complete the intervention in 80% of all recruited participants.
Supplement adherence rate	Symptom diary.	
	Change in RBC total LCn-3PUFA content.	≥2% change in total RBC LCn-3PUFA.
	Capsule count at study completion.	≥80% of capsules consumed.
Refusal rate	Number of identified volunteers who decline to participate/randomize.	
Time lost to exacerbation	Symptom diary.	
*Scientific*		
Supplement safety	Reported symptoms from supplement.	
Estimate effect size	Listed scientific outcomes.	A positive moderate effect size (≥0.2) in at least CRP, dyspnea and FEF_25-75_.
Estimate variance	Standard deviations of listed outcomes.	

CRP, C-reactive protein; FEF_25-75_, forced expiratory flow between 25 and 75% of forced vital capacity; LCn-3PUFA, long chain omega-3 polyunsaturated fatty acid; RBC, red blood cell.

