### Data analysis

SPSS version 17 for WINDOWS [International Business Machines Corporation (IBM), New York, USA] will be used for analyses. Data will be cleaned, checking for errors or missing values. Continuous data will be checked for normality of distribution and non-normally distributed data will be transformed where possible. Scatter plots will be used to determine nature/shape of relationships before applying linear regression.

The primary focus of this study is feasibility, which will be analyzed using descriptive statistics and frequency tables. The key feasibility outcomes are:

1. Recruit 40 participants in 52 weeks;

2. Complete the intervention in 75% of all recruited participants;

3. ≥2% change in total erythrocyte LCn-3PUFA and ≥80% of capsules consumed (estimated from remaining capsules);

4. A positive moderate effect size (≥0.2) in at least three scientific outcome measures (between active and placebo groups).

Analysis of variance (ANOVA) with repeated measures will be used to estimate the effect size of LCn-3PUFA versus placebo supplementation on the scientific outcome measures (six-minute walk, pulmonary function tests, questionnaire scores, blood biomarkers of inflammation and symptoms (for example, high sensitivity C-reactive protein, dyspnea and impulse oscillometry)). Progressive Bonferroni corrections will be used to correct for the effects of multiple outcomes. Comorbid status and severity of exacerbations will be assessed as potential confounders using multiple regression analysis.

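### The retention criterion is a bare 75% cut in 40 participants, set at the planning value with no allowance for sampling error, and Table 2 puts it at 80%

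*Protocol article*

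**What the plan says.** All references are to the protocol article.

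- **Sample Size.** The section states "The target sample size for the feasibility study is 40 participants". It cites a recommendation that "a minimum of 30 participants is required to achieve sufficient precision", and links the two figures: "The target sample of 40 enrolled participants will allow completion of 30 subjects, allowing for a 25% participant dropout rate".
- **Data analysis.** "The primary focus of this study is feasibility, which will be analyzed using descriptive statistics and frequency tables". Key feasibility outcome 2 reads "Complete the intervention in 75% of all recruited participants".
- **Abstract, Methods/Design.** The same value appears: "Key feasibility criteria include recruitment of 40 participants in 52 weeks, 75% participant retention rate".
- **Table 2, Feasibility outcomes and criteria.** The retention measure is "Number of participants completing the intervention", but the criterion beside it is "Complete the intervention in 80% of all recruited participants".

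None of these places attaches a confidence interval, tolerance band or intermediate outcome to the retention criterion.

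**The concern.** Feasibility is the declared main purpose of the study, and retention is one of its key criteria. The 75% bar is exactly one minus the 25% dropout allowance used to set the sample size, and it is compared directly with the observed proportion among 40 people. One participant more or fewer then changes the result from met to not met, although the data say almost the same about true retention.

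The Sample Size section justifies 40 by the precision needed for later sample size calculations. It does not discuss how precisely 40 people estimate the feasibility proportions. The Background reports high dropout in COPD intervention trials, so true retention at or below 75% is a realistic possibility. At stake is how well the retention result can inform the decision on a larger trial. The two values for the bar, 75% and 80%, also leave open what counts as meeting the criterion.

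**Working it through.** **Inputs.** Enrolled N = 40, completers wanted 30 and dropout allowance 25% (Sample Size). Retention bar 75% (Data analysis and Abstract) or 80% (Table 2). Assumptions: exactly 40 are recruited, and participants drop out independently with a common probability.

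**Step 1: the plan's own figure.** 30/(1 − 0.25) = 40, and 40 × 0.75 = 30. The stated figure reproduces exactly.

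**Step 2: chance of reaching the bar.** With X completers distributed as Binomial(40, p), the 75% bar needs X ≥ 30 (0.75 × 40) and the 80% bar needs X ≥ 32 (0.80 × 40).

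| True retention p | P(X ≥ 30), 75% bar | P(X ≥ 32), 80% bar |
|---|---|---|
| 65% | 12.1% | 3.0% |
| 70% | 30.9% | 11.1% |
| 75% | 58.4% | 30.0% |
| 80% | 83.9% | 59.3% |
| 85% | 97.0% | 86.5% |

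At p = 75%, the chance of fewer than 30 completers is 1 − 0.584 = 41.6%. The chance of missing the 80% bar is 1 − 0.300 = 70.0%.

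**Step 3: what an observed result says.** Exact (Clopper-Pearson) 95% limits for x of 40 are the 2.5% quantile of Beta(x, 41 − x) and the 97.5% quantile of Beta(x + 1, 40 − x).

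| Completers | Observed | Exact 95% CI | 75% bar |
|---|---|---|---|
| 30 | 75.0% | 58.8% to 87.3% | met |
| 29 | 72.5% | 56.1% to 85.4% | not met |
| 24 | 60.0% | 43.3% to 75.1% | not met |
| 23 | 57.5% | 40.9% to 73.0% | not met |

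The intervals for 30 and 29 overlap almost entirely. The upper limit first falls below 75% at 23 completers.

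**Step 4: does a larger N cure it?** No. With the 75% bar and true retention of 75%, the chance of missing it is 42.0% at N = 44 (33 needed) and 42.3% at N = 48 (36 needed). The cause is the placement of a single cut at the planning value, not the choice of 40.

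**Step 5: non-overlapping zones with a 75% bar.** Met: X ≥ 30. Modify the protocol: X = 24 to 29, below the bar but with an upper 95% limit at or above 75%. Not met: X ≤ 23, upper limit below 75%.

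| True retention | Met | Modify | Not met |
|---|---|---|---|
| 60% | 3.5% | 53.3% | 43.2% |
| 65% | 12.1% | 67.6% | 20.2% |
| 75% | 58.4% | 40.5% | 1.2% |
| 80% | 83.9% | 16.0% | 0.1% |

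At the planning value, a clear *not met* falls from 41.6% under the single cut to 1.2%.

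**The case against.** The strongest reply has five parts.

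- **There is no arithmetic error.** A reader might infer from the 58% that the sample size is miscalculated. It is not: 30/0.75 = 40 is correct, sizing on the expected number of completers is conventional, and the sentence is conditional on 25% dropout. This stands.
- **A miss chance near one half belongs to any cut placed at the true rate.** A reader might take the 42% as a defect of N = 40. Step 4 shows that it is not. Away from 75% the criterion does discriminate, with a pass chance of 12% at 65% true retention and 97% at 85%. The 25% may also be a cautious allowance rather than the expected rate. This stands, so the 42% on its own is not the finding.
- **No stop rule is stated.** A reader might treat 75% as a formal go/no-go decision. The article calls it a key feasibility criterion, one of several, and describes the outcomes as guiding future trials. The Background does tie feasibility to the justification for a larger study, so the result carries weight, but nothing says that a miss ends the programme.
- **Falling just short of 30 costs little.** Thirty is a rule-of-thumb minimum for estimating variability, and 28 or 29 completers would estimate a standard deviation nearly as well. This stands.
- **Intervals and progression zones may sit in a fuller document.** Descriptive statistics do not exclude intervals, so their absence from an article is not in itself an error.

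What the reply leaves untouched is that the article itself states the bar, the N and the reading of the result. Together they treat 29/40 and 30/40 as opposite outcomes, and the bar has two different values.

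**Conclusion.** The point holds as a weakness in how a key criterion is placed and read, together with an internal contradiction over its value. The sample size calculation is not in error.

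If true retention equals the planning value, 40 enrolled give at least 30 completers with probability 58%, so 30 is an expectation with no reserve. The 75% cut separates 30/40 (59% to 87%) from 29/40 (56% to 85%), which is no real difference in evidence. Under the 80% bar in Table 2, the planned outcome of 30 of 40 would itself miss the criterion, and at 75% true retention a miss has probability 70%.

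These figures assume exactly 40 recruited and independent dropout. If true retention is 80% to 85%, the chance of missing the 75% bar falls to 16% to 3%.

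A reader might go further and conclude that the next trial's dropout allowance would be wrong, or should be taken from the lower confidence limit. The documents do not say how that allowance will be set, and sizing from the lower limit is a debatable preference, so neither is part of this point. The change is worthwhile and cheap, and it needs no extra participants.

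**What to change.** 1. Reconcile the retention criterion so that the Abstract, Data analysis and Table 2 give one value.
2. In Sample Size, describe 30 as the expected number of completers at 25% dropout, and state the 58% chance of reaching at least 30.
3. In Data analysis, add exact 95% confidence intervals for the retention and adherence proportions to the descriptive statistics already planned.
4. Read retention in non-overlapping zones. With a 75% bar and 40 recruited, for example: met at 30 or more completers; modify the protocol at 24 to 29; not met at 23 or fewer. If 80% is the value kept, the same construction gives met at 32 or more, modify at 27 to 31 (the upper limit at 27 is 81.4%), and not met at 26 or fewer (the upper limit at 26 is 79.4%). If the number recruited differs from 40, recompute the zone limits by the same rule.

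The cost is wording only. The criterion becomes less crisp, with about a 40% chance of landing in the middle zone at 75% true retention under the 75% bar, and the completion statement becomes less favourable.

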### Randomization

Subjects will be randomly allocated by minimization [32,33], based on modified Medical Research Council (mMRC) scale for breathlessness scores, to either the fish oil group or the placebo group. The prognostic factor that will be considered in the minimization model will be mMRC score (0, 1, 2, 3 or 4).

### Dietary intervention

Participants will be required to take six 1 g capsules orally per day for 16 weeks. The fish oil group will consume capsules containing EPAX 6000 TG/N omega-3 concentrate (EPAX, Oslo, Norway). Each capsule contains 600 mg of omega-3 fatty acids, which is specified to contain 200 mg of DHA and 300 mg of EPA. It should be noted that while the recommended upper limit of LCn-3PUFA is 3 g/day [34], a number of studies have used higher doses (3.4 g/day to 6.6 g/day) without any reported side effects [35,36]. The placebo group will receive capsules that are identical in appearance containing corn oil (predominantly comprised of linoleic, oleic and palmitic acids) (EPAX, Oslo, Norway). All capsules are flavored to mask the taste and odor. Participants will continue their usual medical treatment throughout the supplementation period. Self-reported medication and supplement use will be collected pre- and post-intervention.

### Blinding

Capsules will be prepackaged into opaque containers and labeled as A or B with the investigator details and supplementation instructions. A staff member of the NPRC external to the project will determine the computer-generated randomization schedule. Capsules will be securely stored and will be dispensed in opaque containers by the clinical trials pharmacist at the RGH, thus ensuring blinding of both the participants and investigators.

### Anthropometry

Height will be measured to the nearest 0.5 cm using a wall-mounted stadiometer (Seca 240, Seca, Hamburg, Germany) and mass will be measured to nearest 0.1 kg using a calibrated digital precision scale (Wedderburn DS-520, Weddernburn, Australia) at both assessment visits. BMI will be calculated from these data as mass (kg) /height (m)^2^.

### Dietary intake

Total energy, macronutrient consumption, and micronutrient consumption will be estimated at baseline using a 74-item food frequency questionnaire from the Cancer Council of Victoria, Australia [37]. The food frequency questionnaire has been validated [38] for use in human dietary intervention trials. The food frequency questionnaire will be repeated post-intervention to determine whether there were any changes in diet throughout the supplementation period.

### Comorbid status

Comorbid status will be determined using two questionnaires: the Charlson index [39], which weights comorbid diseases based on their association with mortality, and the Rx-Risk comorbidity index [40], which uses drug classifications to determine comorbid diseases. Both have been included because there is no consensus on the best method for quantifying comorbid status; therefore, the suitability of both indices will be assessed.

### Feasibility outcomes and criteria

Within the four domains of feasibility (process, resources, management and scientific) there are specified outcomes in the process and resource domains that will be assessed throughout the study against feasibility criteria (see Table 2).

**Table 2 T2:** Feasibility outcomes and key feasibility criteria

**Outcome**	**Outcome measure**	**Key feasibility criteria**
*Process*		
Recruitment rate	Number of participants recruited per week.	Recruit 40 participants in 52 weeks.
Retention rate	Number of participants completing the intervention.	Complete the intervention in 80% of all recruited participants.
Supplement adherence rate	Symptom diary.	
	Change in RBC total LCn-3PUFA content.	≥2% change in total RBC LCn-3PUFA.
	Capsule count at study completion.	≥80% of capsules consumed.
Refusal rate	Number of identified volunteers who decline to participate/randomize.	
Time lost to exacerbation	Symptom diary.	
*Scientific*		
Supplement safety	Reported symptoms from supplement.	
Estimate effect size	Listed scientific outcomes.	A positive moderate effect size (≥0.2) in at least CRP, dyspnea and FEF_25-75_.
Estimate variance	Standard deviations of listed outcomes.	

CRP, C-reactive protein; FEF_25-75_, forced expiratory flow between 25 and 75% of forced vital capacity; LCn-3PUFA, long chain omega-3 polyunsaturated fatty acid; RBC, red blood cell.

#### Process outcome measures

A number of process outcomes will be assessed throughout the study including participant recruitment and retention, supplement adherence, time lost to exacerbation and participant experiences and perspectives about participating in the study. Participant recruitment and retention will be assessed descriptively by recruitment and refusal rates, while retention will be determined by the number of enrolled participants who complete the study protocol.

Supplement adherence will be assessed in three ways. Firstly, by determining changes from baseline to post-intervention in the LCn-3PUFA content of erythrocytes, as the LCn-3PUFAs are incorporated into erythrocyte membranes in a dose-dependent and time-dependent manner [41]. Secondly, a symptom diary will be used to document self-reported supplementation consumption including whether the capsules were consumed each day, how many capsules were consumed and whether any side effects were experienced such as eructation or heartburn. Thirdly, participants will be asked to return all unused capsules at the completion of the study and the remaining capsules will be counted.

The time lost to exacerbation (change in usual symptoms potentially leading to a change in medication, change in usual activities or unscheduled visit to a doctor) will be determined using a symptom diary in the format of one month per page. The diary enables the assessment of exacerbation frequency and severity during the supplementation period. The number of exacerbation days will be counted from the diary, while an exacerbation severity score will be calculated using methods adapted from those described by Effing *et al*. [42]. Data collected from the symptom diary will be used to determine the frequency of exacerbation, whether periods of exacerbation impact upon supplement consumption and whether periods of exacerbation have a confounding effect on supplementation or study outcomes. This information will be used to determine whether exacerbations during the supplementation period should be an exclusion criterion in a subsequent study.

Participant experience and perspectives will be gathered using a structured telephone interview on exit from the study. The structured interview will have four main sections including: 1) the assessments (for example, opinions about the test battery, use of the symptom diary); 2) the supplement (for example, adherence, symptoms and which arm of the trial they believed they were on, any adverse effects experienced); 3) the trial visits and the trial itself (for example, length of the visits, best and worst things about participating in the trial, participation in future trials); and 4) the participants (for example, behavioral changes during trial and life events external to the trial which could impact on trial outcomes).

### Scientific outcome measures

A number of scientific outcomes have been included in order to determine which are the most appropriate for use in a subsequent study. Scientific outcomes have been selected which reflect stages in the theoretical mechanism cascade from cellular (for example, inflammatory biomarkers) to patient-centered (dyspnea, exercise capacity, quality of life) outcomes. Figure 2 presents the proposed cascade between LCn-3PUFA supplementation and the outcome measures.

**Figure 2 F2:**
[figure not shown]
**The proposed relationship between omega-3 fatty acid supplementation mechanisms and outcomes of interest.** 6MWD, six minute walk distance; CRQ, chronic respiratory questionnaire; FEF_25-75_, forced expiratory flow between 25 and 75% of forced vital capacity; HADS, hospital anxiety and depression scale; IOS, impulse oscillometry; PUFA, polyunsaturated fatty acid.

